### Data collection

Ethical approval has been obtained from the Human Subjects Ethics Sub-committee (HSESC) [HSEARS20180527001] of the Hong Kong Polytechnic University. An information (study aims, procedure and duration) sheet (Additional file 1) will be provided, and a signed consent form (Additional file 2) will be obtained from each participant prior to the data collection by the researcher. The baseline questionnaire (Additional file 3) will then be completed by the participants, and anthropometric data including body height, body weight, waist circumference, hip circumference, BMI and WHR will be measured (Additional file 4). The data will be collected by the researcher in either a University laboratory or the participants’ fire stations at three different time points: T_0_ (baseline), T_1_ (3 months after the completion of the 8-week intervention) and T_2_ (6 months after the completion of the intervention). The participants will be reminded about the follow-up data collection 1 month and 2 days in advance through WhatsApp. All the data will be accessed by the research team only. The data will be stored on the study team’s password-protected computer and external hard disk. Only study team members will be able to access the data. The researcher will input participant data from hard copy questionnaires into statistical software, Statistical Package for the Social Sciences (SPSS; SPSS Inc., Chicago, IL, USA), within 2 weeks after the data collection. The hard copy questionnaires will be placed in the locker. The schedule of enrolment, interventions and assessments is shown in Fig. 2.

**Fig. 2 Fig2:**
[figure not shown]
Schedule of enrolment, interventions and assessments

#### Intervention group

The participants in the intervention group will be required to complete the questionnaire, and their anthropometric data will be recorded. Then they will receive the pamphlet from the researcher at T_0_ and the baseline stage-matched teaching material every 2 weeks through WhatsApp.

#### Control group

Similarly, the participants in the control group will also be required to complete the questionnaire, and their anthropometric data will be recorded. The only difference between the intervention and control groups is that the participants in the control group will receive the pamphlet (the same as for the intervention group) from the researcher at T_0_ only.

### Data analysis

All of the collected data will be cleaned prior to the analysis process. The data analysis will be conducted by a statistician who is blind to the participants’ group allocation. The participants’ demographic characteristics will be presented using descriptive statistics (mean and standard deviation) for the continuous data, including age, body height and weight plus BMI, and percentage frequencies for the categorical data, including gender, marital status and educational level. Inter-relationships between the variables will be assessed using Pearson’s correlation coefficient. Differences between the intervention and control groups on outcome indicators will be compared using *t* tests and chi-square tests for the continuous and categorical data respectively. The effect of time (baseline; 3 and 6 months after the completion of the programme) on the outcome measurements will be investigated using repeated measures analysis of variance (ANOVA). The impact of “baseline stage matching” on “stage of change” and other outcome measures within the intervention group will be compared using the Kruskal-Wallis *H* test and one-way ANOVA. Normality tests will be conducted. If the data are normally distributed, it will be appropriate to use parametric tests such as one-way ANOVA. But if they are not normally distributed, non-parametric tests such as the Kruskal-Wallis *H* test will be used. *P* values of less than 0.01 will be considered as statistically significant for all comparisons. All statistical analyses will be conducted using SPSS version 22.0. Intention-to-treat analyses will be applied. As of now, there is no clear cut-off for the acceptable proportion of missing data in a dataset for statistical data analysis. Questionnaires with missing rates of more than 10% will be regarded as “disqualified” and excluded from the analysis. Various statistical methods will be used to treat missing data, including replacement by means or values from the regression analyses, depending on the amount and type of missing data.

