Furthermore, there may be a gender factor to be considered. Past studies have demonstrated that males and females have different eating habits. This is due at least partly to differences in body size [44]. Gough and Conner (2006) discovered that females were more aware of healthy eating than were males [17, 45]. Food preferences and eating styles have also been found to be gender-related [46]. Since most firefighters are males [47–49], it is vital to understand more about how to improve the eating habits of male firefighters. Since many firefighters work on either “24 hours on, 48 hours off” or “48 consecutive hours followed by 96 hours off” rotations [50–53], they tend to live and work in their fire stations for 24 or 48 h per shift, eating their meals and spending their leisure time together. Some studies have found that, in general, eating habits are affected strongly by social context [54] and are also influenced by peers, especially away from home [55–57]. Furthermore, it has been found that eating habits are different when people have their meals alone or with peers [54]. In order to minimize any potential bias, the peer influence should be controlled.

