### Participants

The participants, firefighting teams’ members from the Hong Kong Fire Service Department (HKFSD), will be recruited from fire stations during their free time by the distribution of promotional pamphlets to firefighters in their corresponding fire stations through their fire station colleagues. When a potential participant expresses his interest to participate in this study, he will receive a detailed information sheet (Additional file 1), consent form (Additional file 2) and baseline questionnaire (Additional file 3). Each fire station will be treated as an individual cluster.

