### Recruitment

The participants will be recruited from more than one fire station, located in different districts in Hong Kong. Convenience and snowball sampling methods will be used for the recruitment. The associated participants will be assigned randomly into either intervention or control groups. All the associated participants will be blinded to their intervention allocation.

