### Sample size

There are no clear definitions or guidelines for estimating the sample size for a feasibility study [98]. According to [99], a sample size of 10–15 in a group will probably be sufficient. The proposed sample size was calculated to be 38, allowing for an estimation of the feasibility proportions of adherence and retention to within at least ±17% [100, 101] using a 95% confidence interval with a power of 80% to detect an effect size of 0.6 [77]. The main purposes of this exploratory feasibility study are to collect data to allow the design and sample size calculation for the CRCT.

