### Randomization

The participating firefighters who fulfil the inclusion criteria are stratified into different clusters on the basis of the location of their fire stations prior to the randomization process. These clusters will be randomly assigned to be either intervention or control groups by using a simple randomization method which involves a set of random numbers generated by a computer. Odd and even numbers will represent the control and intervention groups respectively. In order to minimize the bias in this randomization, this process will be conducted by an information technology (IT) expert who is independent of the research team and has more than 15 years’ experience in this field. Furthermore, this IT expert will be blinded during this process. All the participants will be blinded as well, which means they will not know whether they are in the intervention or control groups.

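### Fire stations are randomised, but the arms are compared with participant-level t and chi-square tests that ignore station, so between-arm p values are too small if the analysed score is correlated within stations

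*Protocol article*

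**What the plan says.** The Participants section of the Protocol article defines the cluster: "Each fire station will be treated as an individual cluster". The Randomization section allocates at that level: "These clusters will be randomly assigned to be either intervention or control groups by using a simple randomization method". The number of stations is not fixed beyond a floor in the Recruitment section: "The participants will be recruited from more than one fire station".

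The Data analysis section names the tests. Differences between the arms on the outcome indicators are assessed with t "tests and chi-square tests for the continuous and categorical data respectively". Two further analyses answer other questions: a repeated measures ANOVA for the effect of time, and Kruskal-Wallis or one-way ANOVA by baseline stage within the intervention group. A p value below 0.01 counts as significant for all comparisons.

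The Background states that "eating habits are affected strongly by social context" and describes crews who live, eat and spend leisure time together at the station. The Sample size section gives the study's purpose: "The main purposes of this exploratory feasibility study are to collect data to allow the design and sample size calculation for the CRCT". The only intraclass correlation mentioned in the article is the rater agreement under Body measurements.

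**The concern.** The randomised unit is the station, but the between-arm tests take the firefighter as the unit. Both tests assume independent observations. If men at one station resemble each other on the outcome, the arm means vary more from trial to trial than the tests allow for, and a chance difference between stations can pass for an effect of WhatsApp. The article predicts this resemblance for eating habits, which are its primary outcome.

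Two things are at stake. The three between-arm research questions under Study aims would be judged at a threshold that does not hold its stated error rate. In addition, the study is meant to inform the sample size of a cluster trial, and none of the analyses named would yield the between-station correlation which that calculation needs.

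**Working it through.** **Inputs from the article.** Sample size 38, read as the total, so 19 per arm; threshold 0.01, taken as two-sided; station as the randomised unit; participant-level t test.

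**Assumed, because the article does not give them.** 2, 4, 6 or 8 stations, half per arm; station ICC 0.01, 0.05 or 0.10; total variance 1.

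**Nominal rate.** With ICC 0 the t test has 36 df and a critical value of 2.719, and rejects 1% of the time, as intended.

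**Exact check for two stations (one per arm, m = 19).**
- True variance of the difference in means: 2 × [ICC + (1 − ICC)/19].
- Variance the t test expects: 2 × (1 − ICC)/19.
- Ratio: 1 + 19 × ICC/(1 − ICC).
- True type I error: P(|t| on 36 df > 2.719/√ratio).

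| ICC | Ratio | 2.719/√ratio | True type I error |
|---|---|---|---|
| 0.01 | 1.19 | 2.49 | 1.7% |
| 0.05 | 2.00 | 1.92 | 6.2% |
| 0.10 | 3.11 | 1.54 | 13.2% |

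**Simulation for 2 to 8 stations.** 40,000 null trials per setting, 38 men, raw-score t test, rejections at 0.01:

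| Stations | Men per station | ICC 0.01 | ICC 0.05 | ICC 0.10 |
|---|---|---|---|---|
| 2 | 19 | 1.7% | 6.1% | 13.1% |
| 4 | 9.5 | 1.2% | 3.2% | 5.9% |
| 6 | 6.33 | 1.2% | 2.2% | 3.9% |
| 8 | 4.75 | 1.1% | 1.7% | 2.9% |

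The two-station row agrees with the exact calculation.

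**Change scores.** The article does not say whether the t tests use raw or change scores. The change from baseline was simulated under the same settings.
- Station effect constant over time: it cancels, and rejection stays at about 1% (0.9–1.1%).
- Half the station variance specific to the occasion (and a within-person correlation of 0.5, also assumed): the inflation returns in full, for example 3.1% with 4 stations at ICC 0.05 and 13.0% with 2 stations at ICC 0.10.

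**Tests that are not between-arm comparisons.** With a station effect constant over time and baseline stage unrelated to station, 20,000 null runs (2, 4 or 6 stations, ICC 0.05 and 0.10) gave rejection at 0.01 of 0.97–1.15% for the time ANOVA and 0.93–1.10% for the stage ANOVA. There was no material inflation.

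**The case against.** The strongest reply is that this is an exploratory feasibility study, condensed into an article, whose first aim is feasibility. That does not remove the point. The article does not leave the between-arm tests to another document: it names them, sets a significance rule for them and poses between-arm research questions.

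Other parts of the reply do stand and limit the point:
- A reader might infer that every planned test is invalid. The documents do not support this. The time ANOVA and the stage tests within the intervention arm are not between-arm comparisons. They would be affected only if station effects varied over time, or if stage clustered by station, and neither has been shown.
- A reader might infer that the planned confidence intervals are too narrow. The Data analysis section plans none. The only interval in the article concerns adherence and retention, under Sample size.
- A reader might take 13% as the expected error rate. It needs two stations and an ICC of 0.10. Two stations are permitted but not stated. At ICC 0.01 the inflation is slight.
- The simulations place half the stations in each arm, which simple odd/even randomisation does not guarantee.
- The corrected test has very little power with few stations, and a station ICC estimated from 38 men will be imprecise.

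**Conclusion.** The between-arm analysis is wrong as written: the article randomises stations, expects peers at a station to eat alike, and then compares the arms as if men were independent. The direction is certain for any positive station correlation in the analysed score; the size is conditional. For raw scores and 38 men in total, true type I error at a nominal 1% runs from near nominal (1.1%, ICC 0.01, 8 stations) to about 13% (ICC 0.10, 2 stations), with 2–6% at ICC 0.05. The stricter 0.01 threshold does not remove the excess. For change scores there is an excess only if station effects vary over time. With one station per arm, no analysis can separate the intervention from the station.

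**What to change.** In the Data analysis section, replace the between-arm t and chi-square tests with one of these:
- a mixed model with a random station intercept (linear, or logistic/ordinal for categorical outcomes) and small-sample degrees of freedom; or
- a t test on station-level summaries, with number of stations minus 2 df.

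State the number of stations, and whether raw or change scores are compared. Report the station ICC with its confidence interval for the main outcomes, and show the later trial's sample size over a range of ICCs, because this estimate will be imprecise. With one station per arm, or too few stations for a meaningful test, report between-arm differences descriptively without p values. The time ANOVA and within-arm stage tests need no change on this ground.

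Cost: wording and analysis work only. The Trial status section reports completion, but reanalysis needs nothing beyond each man's station, which the randomisation already required. The real price is much wider uncertainty and little power. With 4 stations the station-level test has 4 − 2 = 2 df and a critical t of 9.92 at 0.01, against 2.72 for the participant-level test on 36 df. That is acceptable for a feasibility study.

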### Development of questionnaire

A questionnaire (Additional file 3) has been developed on the basis of several studies [26, 27, 107–110]. This consists of six study aspects: (1) Personal information; (2) Working characteristics; (3) Eating habits; (4) Health promotion programme for healthy eating; (5) Stage of change; and (6) Decisional balance and self-efficacy.

The questionnaire includes 11 items to assess the Hong Kong firefighters’ eating habits, especially their fruit and vegetable consumption. These questions are based on a series of eating habit studies [26, 27, 107, 108]. The consumption of fruit and vegetables will be measured by asking: (1) “How often did you consume fruits/vegetables in the past week?” (responses ranging from “Not consumed” to “Seven days”); (2) “Where do you usually have fruits/vegetables?” (three choices are “At home”, “During duty” or “No difference, at home and during duty”); and (3) “On a day you consumed the fruits/vegetables, how much did you take on average on that day?” (in bowls or servings). For eating habits, the questions also included “On average, how many days do you have breakfast/lunch/dinner/night snack (take away included) within a week?” (responses ranging from “None” to “More than 5 days”) and “How about the speed of having meals when you are on duty in the fire station when compared to the meals you eat at home?” (responses ranging from “Slower” to “Faster”).

Thirty-five questions were designed to understand decisional balance. Based on Ma et al. (2003) [110], they address the pros, cons and self-efficacy of eating fruit and vegetables. The decisional balance will be evaluated by asking the participants how important each of the pros and cons is in their decisions to consume recommended amounts of fruit or vegetables, using 5-point Likert scales ranging from 0 (Not at all important) to 5 (Very important). Eight pros and nine cons for fruit intake and eight pros and ten cons for vegetable intake will be used to assess the decisional balance.

Twelve questions were designed to assess self-efficacy by rating, on 5-point Likert scales ranging from 0 (Very difficult) to 5 (Very easy), how difficult or easy the participants find it to eat based on the recommendations in six high-risk situations, for each of the two dietary habits [109].

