Four questions were designed to identify the stages of change in eating fruit and vegetables (i.e. “How many servings of fruits/vegetables the respondent usually consumed each day; intention to eat ≥ 2 servings a day of fruit or ≥ 3 or more servings a day of vegetables; whether the participant had been consuming ≥ 2 servings of fruit or ≥ 3 servings of vegetables for more than 6 months; intention to eat more). The participants will then be asked to state their intentions to have servings of fruit and vegetables by choosing one of five statements, each representing a stage of change: “No, and I do not intend to in the next 6 months” [Precontemplation]; “No, but I intend to in the next 6 months” [Contemplation]; “No, but I intend to in the next 30 days” [Preparation]; “Yes, I have been doing so for less than 6 months [Action]; Yes, I have been doing so for more than 6 months [Maintenance]. These four questions and their related intentions were drawn from De Vet et al. (2006) [109].

Another three questions were developed to assess the Hong Kong firefighters’ points of view about the healthy eating promotion: (1) “Can a healthy eating promotion programme help you to change or understand your eating attitudes and habits?”; (2) “Can a pamphlet on healthy eating alone facilitate you to change or understand your eating attitudes and habits?”; (3) “Can a healthy eating promotion programme delivered through a mobile app facilitate you to change or understand your eating attitudes and habits?” The firefighters will be required to rate these three questions on 4-point Likert scales ranging from 1 “Absolutely cannot” to 4 “Absolutely can”.

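### Stage of change and similar ordered items fall to an order-blind chi-square test between arms, in sparse tables, at roughly a 65% relative loss of power for a five-level item at the plan's own alpha and effect size

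*Protocol article*

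**What the plan says.** All from the protocol article.

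- **Data analysis, between-arm contrast.** Outcome indicators are compared between arms by t tests and "chi-square tests for the continuous and categorical data respectively". The sentence names no third method and does not list which items count as categorical.
- **Data analysis, within the intervention arm.** For the effect of matching by baseline stage, where stage of change is itself an outcome, the text reads: "other outcome measures within the intervention group will be compared using the Kruskal-Wallis". One-way ANOVA is named alongside it.
- **Data analysis, normality rule.** The next sentences say: "If the data are normally distributed, it will be appropriate to use parametric tests such as one-way ANOVA". For the opposite case they add: "But if they are not normally distributed, non-parametric tests such as the Kruskal-Wallis".
- **Data analysis, significance level.** *P* "values of less than 0.01 will be considered as statistically significant for all comparisons".
- **Development of questionnaire.** Stage of change is one of five statements, "each representing a stage of change", from precontemplation to maintenance. Meal speed on duty is rated on a range from slower to faster. Three opinion questions use 4-point scales.
- **Sample size.** "The proposed sample size was calculated to be 38". No number per arm is given.

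**The concern.** Pearson's chi-square on a 2×k table gives the same result however the columns are ordered. It therefore cannot tell a systematic move toward action and maintenance from a scatter of differences with no direction. Direction is what the first research question asks about: whether WhatsApp plus pamphlet changes habits more than the pamphlet alone.

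Two further features make the choice a poor one here. First, with few men and several categories the expected counts are small, and the test becomes conservative at 0.01. Second, the same section analyses stage of change within the intervention arm by methods that do use order, while the randomised contrast gets the method that does not.

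The study is meant to supply data for the design and sample size of a later trial. A chi-square statistic offers no directional effect to carry forward, whereas an ordinal odds ratio or a rank-based effect does.

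**Working it through.** **Inputs.** N = 38, effect size 0.6, 95% confidence and 80% power (Sample size); alpha 0.01 (Data analysis; two-sided assumed, since sidedness is not stated); five stages (Development of questionnaire). Assumed: 19 per arm, no dropout, no clustering, and the category proportions, none of which the article gives.

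**The plan's own figure.**
- Precision: 1.96 × √(0.5 × 0.5 / 38) = 15.9%, which meets the ±17% target.
- Power for 0.6 between two arms, two-sided 0.05: n per arm = 2 × (1.96 + 0.842)² / 0.6² = 43.6, so 44 per arm or 88 in total.
- With 19 per arm: Φ(0.6 × √(19/2) − 1.96) = Φ(−0.11) = 46%. At alpha 0.01: Φ(1.849 − 2.576) = 23%.

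The 80% therefore does not reproduce for a two-arm comparison of 38 men in total. Any between-arm test starts from this low base.

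**Sparseness.** 38/2 = 19 per arm; 19/5 = 3.8 expected per cell if the five stages are equally common. In simulation every five-level table had more than 20% of its cells with an expected count below 5; on average about 65-78% of cells were below 5.

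**Power, proportional-odds shift.** An effect of 0.6 corresponds to log OR = 0.6 × π/√3 = 1.088, so OR = 2.97. There were 40,000 simulated trials per row, comparing Pearson chi-square with the tie-corrected Wilcoxon test. Relative loss = 1 − (chi-square power / rank power).

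| Five stages, 19 per arm | Alpha 0.01: chi-square / rank (loss) | Alpha 0.05: chi-square / rank (loss) |
|---|---|---|
| Even (20% each) | 7.3% / 20.8% (65%) | 24.7% / 44.8% (45%) |
| Early (40/25/20/10/5%) | 7.1% / 21.4% (67%) | 24.2% / 44.9% (46%) |
| Middle (15/30/30/15/10%) | 6.8% / 20.8% (67%) | 23.4% / 44.8% (48%) |

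**Power, latent normal shift.** Five equal categories, alpha 0.01, 8,000 runs: 5.8% against 17.5% at 0.6 SD (loss 67%), and 25% against 54% at 1.0 SD (loss 54%).

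**Size.** With no effect, chi-square rejected in 0.3-0.7% of runs at a nominal 1% across the five- and eight-level tables, so it is conservative. In the latent normal runs the rank test rejected in 0.8-0.9%.

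**Where the loss changes.**
- Arms of 12 and 26, alpha 0.01: 52-69%.
- 38 per arm, alpha 0.01: 48-50%.
- OR of 10, alpha 0.01: about 30-34%.
- Three levels, OR 2.94, alpha 0.01: 12.6% against 18.8%, a loss of about a third. The article does not give the number of levels for meal speed; if it is three, this is the relevant figure.

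**The case against.** **The article never sends stage of change to chi-square by name.** True. Its only listed categorical variables are demographic. Chi-square for stage of change is the natural reading of a two-way split into continuous and categorical, not a stated rule.

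**A rank test is already in the section.** With two groups, Kruskal-Wallis is the Wilcoxon test, and the normality rule could be read as covering the between-arm contrast. But that rule follows the within-intervention comparison and names neither the t test nor chi-square. Even read broadly, a normality test does not redirect data already classed as categorical. The objection shows that the scope is unclear; it does not remove the problem.

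**Stronger readings that a reader might infer.**
- *That the days-per-week item, "How often did you consume fruits/vegetables in the past week", is also lost to chi-square.* Its answers run from 0 to 7 and can go to the t test as a count. In simulation the t test had 24% power and the rank test 22%, so nothing is lost.
- *That half or more of the power is always lost.* The figures above show that this depends on alpha, the number of levels and the effect size.
- *That choosing between ANOVA and Kruskal-Wallis by a normality test also ignores order.* It does not; both use order. The complaint there is only that the scale of an ordinal item is known beforehand and needs no normality test.
- *That most outcomes are affected.* Amounts in servings, and the decisional-balance and self-efficacy item sets if scored as scales, need not be.

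**A better test does not rescue the comparison.** This stands. At an effect of 0.6 and alpha 0.01, about four in five true shifts would be missed by the rank test too, and this is an exploratory feasibility study.

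**Conclusion.** The point holds for ordered categorical outcomes, chiefly stage of change, with meal speed and the 4-point ratings as lesser cases. The stated between-arm test ignores their order in sparse tables. For a five-level item at alpha 0.01 and effect size 0.6 it has about 6-7% power against 17-21% for a rank test, a relative loss of roughly 65%. At alpha 0.05 the loss is 45-48%.

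This rests on 19 men per arm, which is inferred from 38 and not assured when whole stations are allocated by simple randomisation. It also rests on assumed category proportions, a uniform shift, and no clustering. It is a weakness in a method that the article does state, and worth correcting. It does not show that the comparison would otherwise be adequately powered.

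**What to change.** In Data analysis:

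1. List the ordered categorical outcomes. For these, replace chi-square with a rank-based (Wilcoxon or Kruskal-Wallis) or proportional-odds comparison between arms, and report a directional effect with its confidence interval.
2. Fix the method in advance by the scale of each item, not by a normality test.
3. Keep an exact test for unordered items such as the usual place of eating.
4. Make the analysis respect fire station, since an ordinary rank or ordinal test would ignore the clustering just as chi-square does.

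**Cost.** No new data are needed. The proportional-odds model adds an assumption, and with a station random effect it may be unstable on 38 men. A station-level permutation test is limited when stations are few: with 4 against 4 there are 70 allocations, so the smallest two-sided *P* is 2/70 = 0.029, which cannot reach 0.01. The article says only that more than one station will be used, so the number of stations must be known before this route is chosen.

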### Study aims

This study has two aims. The first is to determine the feasibility of using a TTM-based printed promotion pamphlet and delivering it with stage-matched teaching materials through WhatsApp to promote healthy eating. The second is to evaluate the potential effects of WhatsApp as a vehicle to promote healthy eating habits in firefighters in Hong Kong. The desired primary outcome is changed eating habits, while the secondary outcomes are body mass index (BMI) and waist-to-hip ratio (WHR).

The following research questions have been set: (1) Will the use of the TTM-based promotion pamphlet and WhatsApp bring about greater changes in their eating habits than the use of the TTM-based pamphlet alone? (2) Will the use of the TTM-based promotion pamphlet and WhatsApp lead to greater changes in the firefighters’ BMIs than the use of the TTM-based pamphlet alone? (3) Will the use of the TTM-based promotion pamphlet and WhatsApp change the firefighters’ WHRs more than the use of the TTM-based pamphlet alone?

In order to address two of the “areas of focus” of a feasibility study (Implementation and Practicality), two more research questions have been posed: If the use of WhatsApp helps to improve firefighters’ eating habits, will this also reduce their BMIs and WHRs and increase their fruit and vegetable intake? Will firefighters find this intervention more useful and efficient than the TTM-based promotion pamphlet?

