## Methods/design

### Study design

A two-armed, pre-post test, clustered randomized control trial (CRCT) design will be used in this study. Figure 1 shows the overall design. The data will be collected at three time points: T_0_, baseline; T_1_, 3 months after the completion of an 8-week intervention; and T_2_, 6 months after the intervention.

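### Questions 1–3 ask about greater change with WhatsApp, but the plan names no between-arm comparison that uses baseline, and its time effect cannot answer them

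*Protocol article*

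**What the plan says.** The three main research questions in the Study aims section compare the arms on change. The first is whether pamphlet plus WhatsApp will "bring about greater changes in their eating habits than the use of the TTM-based pamphlet alone", the second whether it will "lead to greater changes in the firefighters’ BMIs than the use of the TTM-based pamphlet alone", and the third whether it will "change the firefighters’ WHRs more than the use of the TTM-based pamphlet alone". The same section adds: "The desired primary outcome is changed eating habits". The Study design section states: "A two-armed, pre-post test, clustered randomized control trial (CRCT) design will be used in this study". Measurements are taken at T0, T1 (3 months after the 8-week programme) and T2 (6 months after it).

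The Data analysis section names three analyses that bear on this:
- Between arms: "Differences between the intervention and control groups on outcome indicators will be compared using" t tests for continuous data and chi-square tests for categorical data. It does not say at which time point, or whether the indicators are values or changes.
- Over time: "The effect of time (baseline; 3 and 6 months after the completion of the programme) on the outcome measurements will be investigated" by repeated measures ANOVA. No group factor and no group-by-time term is mentioned.
- Within one arm: "The impact of “baseline stage matching” on “stage of change” and other outcome measures within the intervention group will be compared" by Kruskal-Wallis or one-way ANOVA.

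The significance threshold is 0.01 throughout. The Intervention group and Control group sections give both arms the same pamphlet at T0.

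**The concern.** The questions call for a difference between arms in change. The one longitudinal analysis is aimed at a different quantity, the average change over time. The pamphlet carries the same content as the WhatsApp material, so the control arm may well improve too. A time effect could then appear when WhatsApp adds nothing, and it could be absent when the arms move in opposite directions.

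That leaves the between-group tests to answer questions 1–3, and no baseline term is attached to them. A comparison of follow-up values carries whatever baseline difference chance has produced, which can be sizeable when a small number of stations is randomised. It also gives up precision that the T0 measurement could supply in a trial that has little to spare.

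**Working it through.** **The plan's own figure.** The Sample size section gives 38, with ±17% precision and 80% power for an effect size of 0.6. The half-width with n = 38 at a proportion of 0.5 is 1.96 × √(0.25/38) = 15.9%, so ±17% is met. The power statement does not reproduce for a two-group comparison: d = 0.6 with 80% power at two-sided 0.05 needs 44 per arm by the normal approximation. The present point does not rest on that discrepancy. The figures below take 38 as the total, 19 per arm, which the article does not state.

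**Other inputs.** d = 0.6 in units of the follow-up SD; α = 0.01 (Data analysis), taken as two-sided. The baseline–follow-up correlation r is not given, so 0.5 to 0.75 is assumed. The nearest figure in the article is the two-week test–retest mean of 0.75 in ten firefighters, which is only a rough guide to a correlation over several months.

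**Step 1: what the time effect detects.** Two calculations assume no arm difference or a pure arm difference.
- Both arms improve by 0.4 SD (assumed), WhatsApp adds nothing. A paired test on 38 people has standardised effect 0.4/√(2(1−r)), that is 0.40 at r = 0.5 and 0.57 at r = 0.75. It reaches p < 0.01 in 41% and 77% of trials.
- Simulation with 4,000 runs per scenario, 19 per arm, three time points, r = 0.75, no clustering, α = 0.01:

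| Scenario | Time effect | Group × time | Follow-up t test |
|---|---|---|---|
| Both arms improve 0.6 SD | 99.8% | 0.8% | 0.9% |
| Arms move −0.3 and +0.3 SD | 0.5% | 53% | 20% |

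The time effect responds to shared improvement and misses a divergence around zero.

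**Step 2: what the follow-up t test estimates.** Randomisation makes the expected baseline means equal, so the expected arm difference in change equals the expected arm difference at follow-up. The target is right. In a single trial, the chance baseline difference has SD √(2/19) = 0.32 SD units. With 4 stations and an intracluster correlation of 0.10 (both assumed), the mean cluster size is 9.5, the design effect is 1 + 8.5 × 0.10 = 1.85, and the SD becomes 0.32 × √1.85 = 0.44.

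**Step 3: precision given up.** Adjusting for baseline multiplies residual variance by 1 − r²; a change score multiplies it by 2(1 − r). The effective standardised difference is 0.6 divided by the square root of that factor. Power is from the noncentral t distribution with 36 degrees of freedom, α = 0.01, clustering ignored:

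| Analysis | r = 0.5 | r = 0.75 |
|---|---|---|
| Follow-up value only | 21% | 21% |
| Change score | 21% (factor 1.00) | 47% (factor 0.50) |
| Baseline-adjusted | 30% (factor 0.75, d = 0.69) | 54% (factor 0.44, d = 0.91) |

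If 38 were per arm, the normal approximation gives Φ(0.6√19 − 2.576) = 52% unadjusted, and 67% to 92% adjusted.

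**Step 4: with clustering.** Under the 4-station, 0.10 scenario, with 2 degrees of freedom and the intracluster correlation assumed unchanged by adjustment, power at 0.01 is about 3% unadjusted and 3% to 5% adjusted. At 0.05 it is 13% and 16% to 23%. The direction of the gain holds, but its absolute size shrinks sharply.

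**The case against.** The strongest reply is that the plan does contain a between-arm test, that the test estimates the right quantity in expectation, and that a condensed article may leave model terms to an analysis plan. This largely stands, and it limits the point in several ways.

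- A reader might infer that the baseline data go unused. They do not: baseline is a level of the repeated measures ANOVA, and baseline stage is analysed within the intervention arm. What can be said is that no stated between-arm comparison uses baseline.
- A reader might infer that nothing in the plan can answer questions 1–3. Step 2 shows that a follow-up comparison between arms addresses them, though inefficiently.
- That the t tests are unadjusted is the natural reading, not an explicit statement. The indicators could be change scores, since the primary outcome is described as changed habits. Even then the article does not say so, and the change score does no better than the follow-up value at r = 0.5.
- A reader might infer that the time effect is the criterion for success. The article does not make it one. The Step 1 percentages become false claims of WhatsApp benefit only if a time effect is reported as an arm effect.
- The absence of one named eating outcome and time point is a separate matter. A multiplicity figure would need a number of independent tests that the article does not specify, so none is used here.

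The aim is also exploratory: the Sample size section says the study mainly serves the design of a later trial. That lowers the severity. It does not remove the point, because the article poses comparative questions and states which effect the longitudinal analysis will examine.

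**Conclusion.** The point holds in a limited form. Questions 1–3 concern a between-arm difference in change; the plan names between-group tests with no baseline term and a longitudinal test of time alone. The time effect cannot answer the questions. A follow-up t test can, at a cost: about 21% power against 30% to 54% with baseline adjustment. These figures assume 19 per arm, d = 0.6, two-sided 0.01, r of 0.5 to 0.75 and no clustering. They should not be read as the gain this trial would achieve, because with few stations both are much lower and the absolute difference is small. The correlation, the number of stations and the intracluster correlation are all assumptions. Severity: should fix.

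**What to change.** For each continuous outcome, state that questions 1–3 are answered by the arm difference at a named follow-up time (T1 or T2). Take it from one model of the follow-up values on arm, time, arm × time and the T0 value, accounting for station and for repeated measures on the same participant. Report the estimate with its confidence interval. Describe the main effect of time as descriptive and say that it is not evidence for WhatsApp over the pamphlet. A group-by-time test or an explicit change-score comparison, also allowing for station, would be an acceptable alternative, but baseline adjustment is at least as efficient.

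The cost is wording and analysis time only, since all the variables are scheduled at T0, T1 and T2. The Trial status section reports completion on 29 February 2020, so the clarification should be dated and should say whether it was made before outcomes were seen by arm.
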